### Ethical considerations

The research protocol was examined by the accredited regional Medical Research Ethics Committee ‘METC Brabant’, and concluded that participants are not subjected to any procedure or imposed to perform any behavior. With this conclusion the obligation to fulfill the specific requirements of the Dutch law for Medical Research involving Human Subjects (WMO) was waived (reference: NW2014-03). The science committee of the initiating hospital has approved the study protocol (reference: WB/mt/14.030). All participating patients will sign an informed consent form.

## Discussion

This study investigates the effect of an interactive, web-based, treatment decision aid for early-stage prostate cancer. It compares impact on the decision-making process and patient-reported outcomes from an intervention group with a control group. Included patients will be followed for 12 months to investigate long-term consequences from the intervention on regret, treatment satisfaction and quality of life. Randomization will take place at the hospital level, meaning that once included, all patients within in one hospital receive the same treatment. Compared to randomization on the level of the patient, this design is less prone to contamination bias. The strength of this study is the initial involvement of 19 participating hospitals. With this large number, a proper variation of local circumstances can be taken into account that might affect structural adaptation of the DA in clinical practice. The large number of participating hospitals also requires careful management by the researchers during the trial period. Motivating all involved doctors, nurses and assistants requires careful monitoring of inclusion progress per location and adaptation to specific circumstances. Another challenge is to take the treatment variation per hospital into account. If past-year treatment characteristics appear to be imbalanced between both arms, we may decide to adjust for past year treatment, based on hospital-specific treatment profiles obtained from the Netherlands Cancer Registry.

Although we are aware of the fact that individual differences between clinicians could also affect decision outcomes, there are some considerations that justify taking the institution as the unit of analysis. First, diagnosis and offered treatment plans are often the result of multi-disciplinary consideration (for example, urologists, radiotherapists, and oncologists). Secondly, specialization often leads to some clinicians seeing the majority of PrCa patients within an institution. Taking the clinician as unit of analysis could lead to too small clusters in some cases. On the other hand, clinician specialization could also lead to patients visiting multiple clinicians within a hospital before a final decision is made, making it difficult to attribute a treatment decision to a certain clinician. Third, information provision and decisional support is often provided by specialized (oncology) nurses. Typically they assist more than one clinician, which could contaminate individual clinicians’ data. Finally, regional variation in treatment practices, which is expected to be influenced by DAs as explained in previous sections, is generally reported at the hospital level. This indicates that there are influences at the hospital level driving practice variation that go beyond individual differences between clinicians within a hospital. The reported variation in selected treatments between hospitals is available for hospitals included in our study, though no data is available on individual clinician’s variability.

While carefully designed and reviewed by experts, some content of the DA can remain the subject of discussion among healthcare providers. As every urologist, radiotherapist or nurse can be seen as an expert on prostate cancer from their own perspective; all have their own preference in formulating and presenting options, facts and risks involved to prostate cancer and its treatment alternatives. The original DA is tested thoroughly and documented for the topics that should be addressed in the DA, which we have taken over [23, 24]. All adjustments that were made to adjust the DA to Dutch clinical setting are based on the IPDAS criteria [25] for DA development. All textual content is derived from Dutch and European treatment guidelines.

A potential limitation of our DA is that a device with internet connection is needed to use the DA, which could affect our sample and consequently our findings. Although we are aware that this could be a relevant issue in many regions in the world, we do not expect biased results in our trial. The World Bank has estimated internet access in The Netherlands is among the highest in the world, with 94 % of the households (2013) having internet access (www.worldbank.org). Even in older age groups (65 to 75 years) regular internet access is at 80 %, and this percentage is rapidly increasing (2013, Statistics Netherlands). Internet is routinely referred to as part of information provision in standard care. As most of our questionnaires (in both groups) are sent via email, internet access and the ability to use it is also required in both groups, assuring group comparability on this matter.

Our trial has defined decisional conflict as primary measure. As previously mentioned, the DCS is a widely accepted and applied measure in DA evaluations. However, the DCS is also subject to some discussion in the literature about its usefulness as outcome measure in DA evaluations [68]. This is mainly due to its limitation to identify a good decision as a person’s underlying sensitivity to uncertainty may not be fully represented in a high or low decisional conflict score. For example, a high score on the DCS could also represent the effort that one takes to be involved in the decision-making process and absorbing all available information and therefore becoming aware of the difficulty of the decision. Although we are aware of this potential limitation of the DCS, we believe decisional conflict represents the best available affective-cognitive outcome measure that captures the uncertainty involved to prostate cancer treatment decision-making. Uncertainty about disease progression, treatment success and side-effect impact are key elements of the decision-making process in prostate cancer care. Preliminary investigations prior to the current study taught us that decisional conflict levels are substantial; we expect that our DA will be able to reduce these levels and that this potential reduction is meaningful. For meaningful interpretation of our effects we also have additional outcome measures available that can support our findings or can indicate bias if present. Many of our secondary measures focus on the decision-making process (knowledge, satisfaction with information provision, decision-making role) rather than the outcome in terms of a ‘good’ or ‘bad’ decision, this ensures that our conclusions on the usefulness of the DA will not solely depend on interpretation of the DCS.

On a broader level, this study will augment the current paucity of information regarding the implementation of DAs in (Dutch) routine clinical practice, its impact on the treatment decision-making process and long-term effects. This will help patients and clinicians to establish optimal patient-treatment fit. As we hypothesized the effects could involve improved patient involvement and knowledge resulting in higher decision and treatment satisfaction and ultimately reduce regret and improve quality of life.

Finally, the results of this project will contribute to the increasing awareness of shared decision-making and improving patient centered care in the treatment of prostate cancer. This study can provide the scientific evidence needed to include the use of a DA in the prostate cancer treatment guidelines.

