### Randomization

Nineteen Dutch hospitals have been randomized to either ‘usual care’ (arm 1) or ‘usual care + DA’ (arm 2). With this so-called prerandomization, the conventional sequence of obtaining informed consent followed by randomization is reversed [29]. This prerandomization is needed because we make clinicians aware (when introducing the DA) of the principles of shared decision-making and the characteristics of the DA. This could affect the control group if they were recruited within the same hospital.

To prevent potential imbalance between the two arms that could arise from hospital characteristics (for example, hospital size and treatment profile), two strata were included in the randomization procedure. First, if cooperation between two hospital locations leads to overlap in medical staff or patients visiting both locations, there is a risk for contamination bias if these hospital locations are not in the same cluster. In our sample, four pairs of hospitals have this overlap in hospital staff or patient visits. To maintain variability in hospital characteristics within each cluster, only two pairs were allowed to enter the same cluster. The second criterion is related to hospital specific treatment variation. In The Netherlands, hospitals that perform robot-assisted radical prostatectomy indicate a significant larger proportion of their patients for surgery compared to other hospitals [4]. At the moment of randomization, three hospitals from our sample are known for having robotic surgery facilities to treat prostate cancer patients, and only two of these hospitals were allowed to join the same cluster.

Randomization was performed by a statistician not involved in the study and blind to the identity of the hospitals, using SPSS version 19.0 (Statistical Package for Social Sciences, Chicago, IL, USA). As a first step, the four paired hospitals were randomized (block size = 2). Next, the remaining 11 hospitals were also block randomized (block size = 6, with the last position unused). A set seed was chosen that fulfilled to the criteria that only two robot facilitated hospitals were allowed into the same cluster. The generated group order was then applied to a pre-existing list of participating hospitals, which was sorted in alphabetical order. As there is an uneven number of hospitals participating in this study, the largest cluster that was formed was identified as the intervention cluster.

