### Statistical analysis

All analyses will be conducted using SPSS version 19.0 (Statistical Package for Social Sciences, Chicago, IL, USA). A 0.05-significance level will be adopted in all statistical tests.

We will perform a descriptive statistical analysis of organizational (hospitals) and socio-demographic (patients) characteristics in order to assure the comparability of the intervention and control groups. Baseline measures and changes in outcome variables over the study period for each study arm will be presented as means (± SD).

The main outcome decisional conflict is measured at T1 and will be compared between both groups (intervention and control). Multilevel modelling will be carried to take the hierarchical structure of the data into account by specifying random effects at both hospital and patient level. The least square mean proportions will be estimated and compared to assess the effect of the DA on decisional conflict.

The secondary outcomes will also be compared between both groups using multilevel modelling. Some of the secondary measures consist of repeated measures (for example, HRQoL and decisional regret) and will be treated according the appropriate mixed-model approach; that is, repeated measures anova/ancova will be used for outcomes with two time points (decisional regret, treatment satisfaction), and a random coefficient approach will be used for outcomes with three time points (HRQoL) [67]. Observed variation in treatment choice during the trial period will be compared between groups and at level of the individual hospital. For this second comparison, each hospital’s particular historical treatment variation profile (2008 to 2012) will be obtained from the Netherlands Cancer Registry.

Potentially confounding variables (for example, personality, health skills, and age) will be explored for their impact on the primary and secondary outcomes. Missing data and drop-outs will be described.

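### Adjustment for hospital treatment profile is optional and hangs on observed imbalance, and the described models do not carry the robot-surgery factor that restricted the allocation

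*Protocol article*

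**What the plan says.** **Allocation (Protocol article, Randomization).** To prevent imbalance in hospital characteristics, "two strata were included in the randomization procedure".

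- The first concerns four pairs of hospitals that share staff or patients: "only two pairs were allowed to enter the same cluster".
- The second concerns three hospitals with robotic surgery: "only two of these hospitals were allowed to join the same cluster". The stated reason is that such hospitals "indicate a significant larger proportion of their patients for surgery compared to other hospitals".
- The number of hospitals is odd, and "the largest cluster that was formed was identified as the intervention cluster". In this section, cluster means trial arm.

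**Analysis (Statistical analysis).** Decisional conflict is compared in a multilevel model "by specifying random effects at both hospital and patient level", and secondary outcomes are handled similarly. Neither restriction factor is named as a term. The covariates given as examples (personality, health skills, age) are to be explored. For the hospital-level comparison of treatment variation, each hospital's "particular historical treatment variation profile (2008 to 2012) will be obtained from the Netherlands Cancer Registry".

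**Adjustment (Discussion).** "If past-year treatment characteristics appear to be imbalanced between both arms, we may decide to adjust for past year treatment", using hospital profiles from the same registry.

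**The concern.** The adjustment sentence has two layers of discretion: an undefined trigger (imbalance that appears) and an optional response. It does not say which outcomes it covers, or that the decision comes before outcome data are seen. A reader of the final report could not tell whether the adjusted or the unadjusted estimate was the planned one.

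Nothing requires this deferral. The hospitals are already randomised, robot status was known at that time, and the registry years 2008 to 2012 precede the August 2014 start.

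The protocol itself identifies robot facility as a predictor of surgery. A hospital random intercept accounts for correlation within hospitals, but it does not remove a known difference between arms in a prognostic hospital factor. Treatment choice is part of the main objective (Objectives and hypothesis), so the comparison most exposed is not a marginal one.

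**Working it through.** **1. The plan's own power figure.** Inputs from Sample size calculation: effect size 0.50, alpha 0.05 (two-sided assumed), ICC 0.01, 19 hospitals of 20 patients. The 10 v 9 split follows from Randomization: two pairs per arm give 4 v 4 hospitals, and the other 11, in blocks of six with the last place unused, give 6 v 5.

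- Design effect = 1 + (20 − 1) × 0.01 = 1.19
- SE = √[1.19 × (1/200 + 1/180)] = 0.112; 0.50/0.112 = 4.46
- Power = 0.994 (normal) or 0.987 (noncentral t, 17 df)

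The plan states 0.80, which these inputs do not reproduce. That is a separate matter; here 0.987 serves only as the starting value for the cost in step 6.

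**2. Robot split.** Three hospitals with at most two per arm must fall 2:1. Which arm has two is not stated.

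- Two in intervention: 2/10 − 1/9 = 20.0% − 11.1% = 8.9 points
- Two in control: 2/9 − 1/10 = 22.2% − 10.0% = 12.2 points

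**3. Shift in the treatment-choice comparison.** The documents give no figure for the surgical excess. Assuming 20 to 30 points and equal numbers of patients per hospital, the shift runs from 8.9 × 0.20 = 1.8 to 12.2 × 0.30 = 3.7 percentage points with no effect of the decision aid.

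**4. Effect of omitting the term on the test.** Simulated regression of 19 hospital means under the restricted allocation, ICC 0.01, 20 patients per hospital, robot hospitals placed among the 11 unpaired ones. Robot and pair effects are assumptions. Power is at d = 0.3, because at 0.50 it is near its ceiling. There were 6,000 runs for type I error (Monte Carlo SE √(0.05 × 0.95/6000) = 0.003) and 3,000 for power (√(0.7 × 0.3/3000) = 0.008).

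| Robot effect (SD) | Pair effect SD | Type I error: no term / robot / robot + paired yes-no | Power: no term / robot / robot + paired yes-no |
|---|---|---|---|
| 0 | 0 | 0.047 / 0.050 / 0.048 | 0.72 / 0.72 / 0.71 |
| 0.25 | 0 | 0.043 / 0.052 / 0.052 | 0.65 / 0.70 / 0.69 |
| 0.50 | 0 | 0.026 / 0.053 / 0.052 | 0.49 / 0.70 / 0.69 |
| 0 | 0.2 | 0.074 / 0.072 / 0.074 | 0.62 / 0.60 / 0.60 |
| 0.50 | 0.2 | 0.045 / 0.075 / 0.076 | 0.44 / 0.60 / 0.60 |

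Without pair effects, omitting a robot effect makes the test conservative and loses power. Including the term when there is no robot effect costs almost nothing.

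**5. Pairs.** Paired hospitals number 4/10 v 4/9, nearly balanced, so a paired yes/no term has little to correct. The randomisation text implies that each pair was allocated together, giving 4 + 11 = 15 independent units. If pairs share an effect, the yes/no term does not help: type I error stays at 0.074 in the fourth row. The assumed pair variance, 0.2² = 0.04, is four times the planned hospital variance of 0.01, so this row is an illustration and not an estimate.

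**6. Cost of adjusting, at d = 0.50 and ICC 0.01.**

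- One or two hospital-level terms (df 17 to 16 or 15): power 0.9874 to 0.9868 or 0.9861
- Each pair as one cluster of 40: design effect 1 + 39 × 0.01 = 1.39. Effective sizes are 2 × 40/1.39 + 5 × 20/1.19 = 141.6 and 2 × 40/1.39 + 6 × 20/1.19 = 158.4. With 13 df, power is 0.979
- Pairs as clusters plus two terms (11 df): 0.975

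**The case against.** **The covariate list.** A journal article need not list fixed effects, and an analysis plan that is not shown may add robot facility. This stands: the missing terms alone would not be a finding. It does not reach the Discussion sentence, which states a rule and leaves it open.

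**The 2:1 split.** A reader might infer that the restriction created an imbalance. It did not: three hospitals cannot be split better than 2:1, and the restriction rules out 3:0. The remaining difference is a reason to adjust, not a fault in the randomisation.

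**The 0.05 level.** A reader might infer that choosing adjustment after seeing imbalance makes the primary test anti-conservative. The documents do not support this. The trigger is pre-trial registry data rather than trial outcomes, and omitting a robot effect lowers the type I error (0.043 or 0.026 in step 4). The only values clearly above 0.05 come from an assumed shared pair effect.

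**Relevance to each outcome.** No text says that robot facility affects decisional conflict; for that outcome the term is a matter of precision. The stated choice hypothesis concerns variation in treatments, not the surgical rate, and the planned comparison with each hospital's own history addresses standing differences in part. Both points stand and limit the weight of the shift in step 3.

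**The registry period.** Past-year in the Discussion and 2008 to 2012 under Statistical analysis might be read as a contradiction. The latter is tied to a different comparison, and nothing says it is the only extract. The covariate's period is unclear; a contradiction is not proven.

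**Conclusion.** The point holds in limited form. The Discussion makes adjustment for hospital treatment profile optional and dependent on observed imbalance, and the models as described do not carry the robot-facility factor that restricted the allocation. Adjusted and unadjusted analyses therefore both remain open, and precision and balance are given up, chiefly in the treatment-choice comparison.

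The size is modest. A shift of about 2 to 4 percentage points in the surgery difference rests wholly on an assumed surgical excess of 20 to 30 points. The power loss (from about 0.70 with the term to 0.65 or 0.49 without it) rests on d = 0.3 and assumed robot effects of 0.25 or 0.50 SD. Inflation of the type I error for decisional conflict is not shown. The change is still worth making, because a fixed rule costs almost nothing.

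**What to change.** Replace the Discussion sentence with adjustment that is fixed in advance and applied whatever the imbalance:

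- Include robot facility (yes/no, as known at randomisation) as a fixed effect in the primary and secondary models.
- In the treatment-choice models, include the hospital's pre-trial registry share of the relevant treatment over one stated period: 2008 to 2012 as already planned, or a later period if available. Let it replace robot status if the two are collinear, which is likely given the protocol's reason for the restriction.
- Represent the four hospital pairs by treating each pair as one cluster, or by a pair-level random effect, and not by a paired yes/no term.

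The cost is analysis wording and one or two cluster-level degrees of freedom: power at the planned effect size goes from 0.987 to 0.987 or 0.986. Treating pairs as clusters alone gives 0.979, also under one point. Both changes together give 0.975, about 1.2 points. No new data are needed if the 2008 to 2012 profile is used.

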## Trial status

This trial is currently recruiting patients. The start date was August 2014. The initial patient inclusion is expected to take twelve months. Patients will be followed for one year.

## Abbreviations

CCCS: Comprehensive Cancer Centre South
CRCT: cluster randomized controlled trial
DA: decision aid
EORTC: European Organization for Research and Treatment of Cancer
HRQoL: health-related quality of life
IPDAS: International Patient Decision Aid Standards
METC: Medical Research Ethics Committee (MREC). In Dutch: Medisch Ethische Toetsings commissie
PrCa: prostate cancer
SDM: shared decision-making
VCM: values clarification method
WMO: Medical Research Involving Human Subjects Act. In Dutch: Wet medisch-wetenschappelijk onderzoek met mensen
